### Blinding

The principal investigators and lead statistician will be blinded to participant randomization. Due to the nature of the intervention, trial participants and oncologists will not be blinded. Additionally, the research coordinators and program manager will not be blinded to treatment allocation. We do not anticipate the need for unblinding, however, any inadvertent unblinding will be reported.

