**Methods:**

We will conduct a multicenter, randomized, assessor-blind, parallel-group, pragmatic, hybrid type 1 effectiveness-implementation trial at three cancer centers across the United States. The DeCIDE PC intervention will be delivered over 6 months with CHW support tailored to the individual needs of the patient and caregiver. The primary outcome will be advance care planning. The treatment effect will be modeled using logistic regression. The secondary outcomes are quality of life, quality of communication, hospice care utilization, and patient symptoms.

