Key Inclusion and Exclusion Criteria	Inclusion criteria for patients: Adult (≥ 18 years old) patients who (1) self-identify as African American, (2) have advanced solid organ malignancy (AJCC stage III or IV), (3) are English speaking, (4) have intact cognition and an ability to provide informed consent, and (5) have not had any palliative care experience within the last year Exclusion criteria for patients include: (1) age < 18 years old, (2) unable to read or comprehend English, (3) unable to provide informed consent, and (4) palliative care experience within the last year Inclusion criteria for caregivers: Adult (≥ 18 years old) caregivers who (1) provide informal (unpaid) care to an eligible African American cancer patient (related or unrelated), (2) are English speaking, and (3) have intact cognition and an ability to provide informed consent Exclusion criteria for caregivers include: (1) age < 18 years old, (2) unable to read or comprehend English, and (3) unable to provide informed consent
Study Type	Type of study: Interventional Study design: Multicenter, randomized, assessor-blind, parallel-groups, pragmatic, hybrid type 1 effectiveness-implementation trial involving patients from three oncology practices in the United States
Date of First Enrollment	September 2023 (anticipated)
Sample Size	Target sample size: 160 patient-caregiver dyads (total 320 participants)
Recruitment Status	Pending: Participants are not yet being recruited or enrolled at any site
Primary Outcome(s)	Outcome Name: Advance care planning Metric/method of measurement: Self-reported or documented Advance Directive or a documented discussion of care preferences between the patient and caregiver or healthcare team Timepoints: Baseline, 2 months, 6 months
Key Secondary Outcomes	Outcome Name: Quality of life Metric/method of measurement: Quality of Life measured by the Functional Assessment of Chronic Illness Therapy - Palliative Care Timepoints: Baseline, 2 months, 6 months
Ethics Review	Status: Approved Date of approval: March 31, 2022
Completion Date	Not applicable
Summary Results	Not applicable
IPD Sharing Statement	Plan to share IPD: Yes Plan description: We plan to make the full protocol, deidentified participant-level data, and the statistical code available from the corresponding author on reasonable request

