### Study design

We will first use a mixed methods approach to refine the DeCIDE PC intervention by addressing multilevel implementation barriers (Aim 1). This stage will involve gathering input from patients and caregivers through patient-caregiver dyad focus groups and eliciting input from stakeholders in oncology, palliative care, and the community through baseline key informant interviews. Additionally, we will initiate annual environmental scans and establish a Community Advisory Board (CAB) at each enrollment site. The site-specific CABs will be comprised of patients, family members, community members, and health system members. We will aim to recruit 8–10 members at each site. The CABs will meet quarterly and will be asked to review and provide feedback on recruitment and retention approaches, data collection procedures, intervention content and delivery, interpretation of results, and dissemination of findings. Following Aim 1, we will evaluate the effectiveness of the DeCIDE PC intervention in improving palliative care outcomes in African American patients with advanced cancer and their informal caregivers compared to enhanced standard of care (Aim 2). This will be accomplished through a multicenter, randomized, assessor-blind, parallel-group, pragmatic, hybrid type 1 effectiveness-implementation trial with a 1:1 allocation ratio. Finally, we will use a mixed methods approach and employ the CFIR (Consolidated Framework for Implementation Research) and RE-AIM (Reach, Effectiveness, Adoption, Implementation, Maintenance) frameworks to evaluate implementation of the DeCIDE PC intervention (Aim 3). This will be achieved through multilevel analysis of intervention delivery and qualitative interviews. An overview of the study design is outlined in Fig. 1. This paper will focus on the protocol related to Aim 2, the randomized controlled trial.

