### Data collection

Data collection will be the responsibility of the research coordinators with oversight from the site principal investigators. Investigators will be responsible for ensuring the accuracy, completeness, legibility, and timeliness of the data collection.

Baseline demographics, medical history, performance status, and disease characteristics will be obtained from EMR review. The remaining data will be gathered from EMR review and surveys administered at baseline (within 1 week of enrollment), 2 months, and 6 months. Research coordinators will administer all surveys by telephone and record responses in the central REDCap database, stored on password protected computers on servers within Johns Hopkins University [37].

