### Oversight and monitoring

The coordinating center for this trial is Johns Hopkins University, School of Medicine, Department of Surgery, and Division of Surgical Oncology. The trial steering committee meets weekly and is comprised of the lead principal investigator, program manager, research coordinator, and lead CHW, as well as a senior research program coordinator and the clinical research program administrator within the Department of Surgery at Johns Hopkins University.

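### The trial is labelled assessor-blind, but the article gives outcome collection to research coordinators it declares unblinded and describes no blinded assessor

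*Protocol article*

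**What the plan says.** The label appears three times in the protocol article. The Abstract (Methods) announces a "multicenter, randomized, assessor-blind, parallel-group, pragmatic, hybrid type 1 effectiveness-implementation trial". Study design repeats it as a "multicenter, randomized, assessor-blind, parallel-group, pragmatic, hybrid type 1 effectiveness-implementation trial with a 1:1 allocation ratio". Table 2, the trial registration data set, has "Multicenter, randomized, assessor-blind, parallel-groups, pragmatic, hybrid type 1 effectiveness-implementation trial involving patients from three oncology practices".

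The Blinding section sets out who is and is not blinded:

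- Blinded: "The principal investigators and lead statistician will be blinded to participant randomization".
- Not blinded: "Due to the nature of the intervention, trial participants and oncologists will not be blinded".
- Not blinded: "Additionally, the research coordinators and program manager will not be blinded to treatment allocation".

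Participant timeline and Allocation have the site coordinators screen, consent, enrol and randomise, and Allocation itself calls them unblinded. Participant timeline then has the same coordinators review the medical record and give the surveys at baseline, 2 months and 6 months. Data collection makes the data their responsibility and adds: "Research coordinators will administer all surveys by telephone and record responses in the central REDCap database".

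Under Outcomes, ACP is met by an advance directive that is either self-reported or documented, or by a documented discussion of care preferences.

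**The concern.** An assessor-blind label tells readers that whoever ascertains the outcome does not know the arm. Here the people who ask the questions and read the charts are the people who performed the allocation.

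The primary outcome is exposed on both routes. The self-report route depends on an interview, where prompting and probing can differ by arm. The chart route depends on how thoroughly a record is searched and which entries are picked out. Community health workers (CHWs) write notes in the record of intervention patients, so the chart itself also carries cues to allocation. The survey-based secondary outcomes, including the principal one (FACIT-Pal), come through the same telephone interviews.

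If the label stands, the trial report and the registration record will claim a protection that the described conduct does not provide.

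**Working it through.** **1. Label against procedure**

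| Task | Who does it | Blinded? | Where stated |
|---|---|---|---|
| Randomise | Research coordinators | No | Participant timeline; Allocation |
| Review the medical record | Research coordinators | No | Participant timeline |
| Give and record all surveys | Research coordinators | No | Data collection; Blinding |
| Report own status | Participants | No | Blinding |
| Lead the statistical work | Lead statistician | Yes | Blinding |
| Oversee data collection | Site principal investigators | Yes | Data collection; Blinding |

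Neither blinded role is described as assessing outcomes. Every described step of outcome collection belongs to an unblinded role.

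**2. The plan's own sample size.** Inputs from Sample size: 30% against 60%, alpha 0.05 (taken as two-sided), power 90%. With pooled variance and no continuity correction,

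n = [1.960 × √(2 × 0.45 × 0.55) + 1.282 × √(0.30 × 0.70 + 0.60 × 0.40)]² / 0.30² = (1.379 + 0.860)² / 0.09 ≈ 55.7, so 56 per arm, and 56 / 0.80 = 70.

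Both stated figures reproduce. The contradiction does not depend on them.

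**3. Illustration of the stakes.** From the article: 30% ACP under control, and 80 enrolled per arm less 20% attrition, so 80 × 0.80 = 64 evaluable. Assumed, with no source in the article: a true 30% in both arms, a false yes in a fraction x of ACP-negative intervention patients, and none among controls.

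Recorded intervention rate = 0.30 + 0.70x.

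The chance of a significant result favouring the intervention is Φ[(d − 1.960 × SE₀) / SE₁]. Here d is the recorded difference, SE₀ = √(2p̄(1 − p̄)/64) with p̄ the mean of the two rates, and SE₁ = √([p₁(1 − p₁) + p₂(1 − p₂)]/64).

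- x = 0.10: 37% against 30%, d = 0.07, SE₀ = 0.0834, SE₁ = 0.0832. Φ[(0.07 − 0.1635)/0.0832] = Φ(−1.12) ≈ 0.13.
- x = 0.20: 44% against 30%, d = 0.14, SE₀ = 0.0853, SE₁ = 0.0844. Φ[(0.14 − 0.1673)/0.0844] = Φ(−0.32) ≈ 0.37.

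The nominal rate in that direction is 2.5%.

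**4. Range.** For a recorded difference of 5, 10, 15 or 20 points with no true difference and 64 per arm, the figures are about 9%, 22%, 42% and 64%. For a 10-point difference they are about 20% with 56 per arm and 26% with 80. The two-proportion test stands in for the planned adjusted logistic regression.

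**The case against.** Several points on the other side are fair.

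- **The article is condensed.** A fuller protocol might name someone who makes the final ACP classification, and the article does not say who does. A reader might infer that no blinded assessor exists anywhere in the trial. The text supports only that none is described. This does not rescue the label, because the article explicitly gives chart review and all surveys to staff it calls unblinded.
- **Participants are unblinded in any case.** Bias in self-reported ACP and in the questionnaires would partly remain with a blinded interviewer. This stands, and it limits what the remedy can achieve.
- **The numbers are assumed.** The false-yes rates have no source, and assuming none among controls is one-sided. They show a mechanism and do not estimate a bias. The direction is likely, not established.
- **The investigators' blind.** A reader might infer that it also fails. The steering committee meets weekly and "is comprised of the lead principal investigator, program manager, research coordinator, and lead CHW", the lead investigator takes part in a monthly 5% case review, and participants are told to report adverse events to that investigator directly. But nothing says that allocation is discussed or displayed in these contacts, and the Blinding section says inadvertent unblinding will be reported. This is a secondary risk, not a contradiction.

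**Conclusion.** The contradiction holds on the face of the article: the label is assessor-blind, and the described assessors are unblinded. The label has to be reconciled with the procedures.

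The consequence for the primary outcome is a possible bias, probably toward the intervention, of unknown size. The figures of 13% and 37% rest on a true 30% in both arms, 64 evaluable per arm, and false-yes rates of 10% and 20% confined to the intervention arm. The documents do not support saying that the result will be biased, or that blinded interviewers would make it free of bias.

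**What to change.** **Required.** Unless outcome ascertainment is actually blinded, replace assessor-blind in the Abstract, Table 2 and Study design with an accurate description: open-label, with the lead statistician and the principal investigators blinded to allocation. This costs wording only.

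**Recommended, where existing site capacity allows.**

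- Have the 2- and 6-month telephone surveys made by a coordinator from another site who did not enrol or randomise the patient, with allocation and CHW fields hidden in REDCap.
- Have ACP chart extracts classified by someone without access to allocation. Hide the authorship of CHW notes but keep their content on care preferences. Deleting the notes could remove genuine documented discussions in the intervention arm only.
- Add a sensitivity analysis restricted to documented ACP.
- State that participants remain unblinded, so self-report bias is reduced but not removed.

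The cost is REDCap access settings, cross-site scheduling, and a narrow exception to the rule under Data management that limits coordinators to their own site's data. The retention procedure also needs thought, since lost contact is partly regained at clinic visits. The article gives no coordinator numbers or workload, so whether this needs extra staff cannot be judged from it. The sample size does not change.

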### Data collection

Data collection will be the responsibility of the research coordinators with oversight from the site principal investigators. Investigators will be responsible for ensuring the accuracy, completeness, legibility, and timeliness of the data collection.

Baseline demographics, medical history, performance status, and disease characteristics will be obtained from EMR review. The remaining data will be gathered from EMR review and surveys administered at baseline (within 1 week of enrollment), 2 months, and 6 months. Research coordinators will administer all surveys by telephone and record responses in the central REDCap database, stored on password protected computers on servers within Johns Hopkins University [37].

### Plans to promote participant retention and complete follow-up

To promote participant retention and complete follow-up, research coordinators will make every effort to remain in contact with study participants throughout their time on the study. If a participant is not reachable within 2 weeks of the baseline, 2-month, and 6-month surveys, the research coordinators will attempt to regain contact through three telephone calls, scheduled visits for clinical care, and if necessary, a letter to the participant’s last known mailing address. These attempts will be documented in the participant’s medical record and study file. If issues with retention occur, these will be brought to the CABs to aid in addressing and correcting these issues.

### Data management

The lead principal investigator and central study team will have access to the data sets from all three enrollment sites. The site principal investigators and research coordinators will only have access to their own site’s data. All electronic data will be stored on password protected computers on servers within Johns Hopkins University. All data collected using paper forms will be stored in a locked filing cabinet within an office assigned to the study team. Study data will be retained in a deidentified manner for 5 years following study completion.

### Confidentiality

We will assign each participant with a study ID, which will be stored securely on REDCap and will only be accessible to the study team. All stored data will be deidentified.

### Plans for collection, laboratory evaluation and storage of biological specimens for genetic or molecular analysis in this trial/future use

This is not applicable to the study.

### Statistical analysis plan

Intention-to-treat analysis will be used with each patient to be included in the group to which they were assigned at randomization regardless of adherence to the intervention or crossover. Descriptive statistics will be performed and presented as means with standard deviations, medians with ranges, or frequencies with proportions, overall and by study arm. To estimate the treatment effect on completion of ACP, we will use a logistic regression model with study arm as the primary predictor and enrollment site and cancer stage (AJCC stage III or IV) as the covariates. The exponentiated coefficient for the study arm will estimate the odds ratio of ACP comparing the intervention arm to the enhanced standard of care arm. Any other covariates that are differentially distributed by study arm will also be included in the model for adjustment. To estimate the treatment effect on QOL, we will use generalized mixed-effects linear regression modeling with a random intercept and robust variance estimate. We will use longitudinal generalized mixed-effects modeling methods for all other secondary outcomes. We will report the effect size, standard error, and 95% confidence interval for the estimate of the treatment effects at 6 months.

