### Sample size

We calculated our sample size to ensure sufficient power to detect a clinically meaningful difference in both our primary outcome (ACP) and our principal secondary outcome (QOL) between the study arms. With an alpha of 0.05 and power of 90%, we estimate a sample size of 56 participant per study arm to detect a 30 percentage point difference in ACP at 6 months, based on effect sizes from previous studies and conservatively assuming that 30% of patients in the enhanced standard care arm will have ACP [26, 36]. After accounting for a 20% attrition rate over the study period, the adjusted final sample size based on our primary outcome is 70 participants per study arm (140 participants total). The sample size calculation based on our principal secondary outcome of QOL, measured by FACIT-Pal, is based on a recent study, which found that palliative care was associated with a standardized mean difference (SMD) in QOL of 0.46 (95% CI 0.08–0.83) [28]. With an alpha of 0.05 and power of 80%, and after accounting for a 20% attrition rate, we estimate a sample size of 80 participants per study arm (160 participants total) to detect a SMD in QOL of 0.5. To ensure adequate power for both outcomes, we will plan to enroll 160 participants. We will seek to recruit a caregiver alongside each patient as a patient-caregiver dyad, but a lack of caregiver participation will not preclude a patient's enrollment. Our total potential sample size for the trial is therefore 320 participants, including 160 patients and 160 caregivers.

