### Allocation

Patient-caregiver dyads will be randomized in a 1:1 ratio into one of two groups, the DeCIDE PC intervention group or the enhanced standard of care group. To yield balanced groups, the random allocation sequence will be computer-generated with a block size of 6. Randomization will be stratified by cancer stage (AJCC stage III or IV). Allocation will be entered into the Research Electronic Data Capture (REDCap) database by a unblinded statistician at the central study site who is not directly involved in the study design, study conduct, or participant enrollment. Randomization will be performed immediately after enrollment by unblinded research coordinators through REDCap.

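### ACP is sized on an absolute difference, but the only named primary effect measure is an odds ratio whose target moves with imbalance-driven covariates; no risk difference with an interval is prespecified

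*Protocol article*

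**What the plan says.** All references are to the protocol article.

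- **Sample size.** The ACP calculation is on the absolute scale. Its aim is "to detect a 30 percentage point difference in ACP at 6 months". The control rate behind it is fixed by "conservatively assuming that 30% of patients in the enhanced standard care arm will have ACP", so the implied intervention-arm proportion is 60%. The result is 56 per arm at alpha 0.05 and 90% power.
- **Statistical analysis plan, effect measure.** ACP is analysed by logistic regression with study arm, enrolment site and cancer stage. The exponentiated arm coefficient "will estimate the odds ratio of ACP comparing the intervention arm to the enhanced standard of care arm".
- **Statistical analysis plan, covariates.** "Any other covariates that are differentially distributed by study arm will also be included in the model for adjustment".
- **Statistical analysis plan, reporting.** Descriptive statistics include frequencies and proportions by arm. An effect size, standard error and 95% confidence interval are promised at 6 months, but that sentence names no scale. The odds ratio is the only measure named for ACP.

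**The concern.** Two features of the stated plan work against each other.

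1. The effect judged worth detecting is a difference in proportions. The only measure named for the primary estimate is a ratio of odds. ACP is expected to be common (30% to 60%), so the odds ratio is well away from the risk ratio. It also translates into different absolute gains depending on the control-arm proportion.
2. The odds ratio is conditional on whatever is in the model, and the plan lets chance imbalance decide part of that list. Because the odds ratio is non-collapsible, adding a prognostic covariate changes the quantity being estimated, even under perfect randomisation. The primary target is therefore not fixed before the data are seen.

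The stake is interpretation. This is a pragmatic effectiveness-implementation trial meant to inform adoption elsewhere. Those deciding on adoption will want the absolute gain in ACP and its uncertainty, and the plan does not commit to an adjusted version of that with an interval.

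**Working it through.** **Inputs.** From Sample size: control proportion p0 = 0.30, difference 0.30, so p1 = 0.60; alpha 0.05 (taken as two-sided, which reproduces the stated figure); power 90%; attrition 20%; enrolment 160. From Allocation: 1:1, so 80 per arm and 80 × 0.80 = 64 evaluable per arm.

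**Step 1. The plan's own figure.** Two-proportion formula, pooled variance, no continuity correction:

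n = [1.960·√(2 × 0.45 × 0.55) + 1.2816·√(0.30 × 0.70 + 0.60 × 0.40)]² / 0.30² = (1.379 + 0.860)² / 0.09 ≈ 55.7, rounded up to 56 per arm.

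Allowing for attrition: 56 / 0.80 = 70 per arm. Both match the document, so the design does rest on a difference in proportions.

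**Step 2. The target on three scales.**

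- Risk difference: 0.60 − 0.30 = 0.30
- Risk ratio: 0.60 / 0.30 = 2.0
- Odds ratio: (0.60/0.40) / (0.30/0.70) = 3.5

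**Step 3. How the odds ratio and the difference map to each other.** For a fixed odds ratio of 3.5, p1 = 3.5·p0 / (1 − p0 + 3.5·p0). For a fixed 30-point gain, the odds ratio is computed from p0 and p0 + 0.30.

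| Control ACP | Gain if OR = 3.5 | OR if gain = 30 points |
|---|---|---|
| 10% | 18 points | 6.0 |
| 20% | 27 points | 4.0 |
| 30% | 30 points | 3.5 |
| 40% | 30 points | 3.5 |
| 50% | 28 points | 4.0 |
| 60% | 24 points | 6.0 |

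From 20% to 50% the gain stays within 27 to 30 points. The mapping departs clearly only towards the extremes.

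**Step 4. Movement of the odds ratio with covariates.** Hold the marginal proportions at 30% and 60%, and let baseline covariates spread the log-odds normally with standard deviation s. The document gives no value for s, so a range is assumed.

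| s | Conditional OR |
|---|---|
| 0 (no covariates) | 3.50 |
| 0.3 | 3.59 |
| 0.5 | 3.76 |
| 0.8 | 4.15 |
| 1.0 | 4.52 |

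The risk difference is 0.30 in every row.

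**Step 5. Precision on each scale at the design point, 64 per arm, unadjusted.**

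- Risk difference: SE = √(0.21/64 + 0.24/64) = 0.0839, so the 95% CI is 0.30 ± 0.164, about 0.14 to 0.46.
- Odds ratio: SE of the log = √(1/(64 × 0.21) + 1/(64 × 0.24)) = 0.3735, so the 95% CI is about 1.68 to 7.28.

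**Step 6. Is the sample size affected?** Powering a Wald test on the log odds ratio gives n = (1.960 + 1.2816)² × (1/0.21 + 1/0.24) / (ln 3.5)² ≈ 59.8, or 60 per arm. That is above 56 but below the 64 expected to be evaluable. Power with 64 per arm on the two-proportion test is about 94%.

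**The case against.** The case on the other side is substantial, and most of it stands.

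- **Proportions by arm are promised.** A reader might infer that the trial will report nothing but an odds ratio and so cannot be compared with its own target. The document does not support this. If the descriptive commitment is applied to ACP at 6 months, subtraction gives a crude difference, and the counts give its interval. The 30 points are also an effect to power for; nothing makes them a threshold the result must reach.
- **The odds ratio is a valid measure.** A reader might infer that the result is bound to look larger than it is. That happens only if 3.5 is misread as a risk ratio, and the document nowhere describes it as one.
- **Sizing on proportions and analysing by logistic regression is routine.** The stated control rate and difference fix the design odds ratio at 3.5. The test and power are not undermined.
- **Choosing covariates by observed imbalance is open to criticism on any scale.** This is true, but the consequence here is specific: on the odds-ratio scale it alters what is being estimated, not only how precisely.
- **A supplementary risk difference could sit in a fuller analysis plan that is not shown.** It could, and its absence alone would not be a finding. What remains is what the article states: the design scale, a different named effect measure, and a covariate rule that leaves that measure's target open.

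**Conclusion.** The point holds as a modest matter of estimand and reporting. The design target is an absolute difference. The only effect measure named for the primary outcome is a conditional odds ratio whose target depends partly on chance imbalance, and no absolute difference with a confidence interval is prespecified.

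Its size: odds ratio 3.5 against risk ratio 2.0 at 30% versus 60%, and a drift to roughly 3.8 to 4.5 under adjustment. The drift rests on the assumed spread of covariate effects (SD 0.5 to 1.0) and would be smaller with weakly prognostic covariates. The ambiguity in absolute gain is slight if control ACP falls between 20% and 50%, and larger outside that band.

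The documents do not support a conclusion that the odds ratio is wrong, that it must be displaced as the primary measure, or that the trial is wrongly sized.

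**What to change.** In the Statistical analysis plan section, make two changes before any outcome data are examined by arm.

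1. **Add the absolute effect.** From the planned logistic model, with covariates fixed in advance as site and stage, predict each patient's probability of ACP at 6 months under each arm. Average these over the trial population and take the difference. Report this standardised risk difference with a delta-method or bootstrap 95% CI, together with the odds ratio.
2. **Close the covariate list.** Remove the rule that adds covariates because they look imbalanced by arm, or limit it to a sensitivity analysis.

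The cost is a sentence or two of text and a few lines of code on a model already planned. It needs no additional patients, visits or data, and the sample size is unchanged. The second change does alter which model counts as primary if imbalances appear, so it should be recorded as a change to the analysis.

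### The primary model adds any covariate that happens to differ between arms, by no stated criterion, so chance and the analyst's reading decide which odds ratio is estimated

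*Protocol article*

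**What the plan says.** The Statistical analysis plan section of the protocol article defines the primary model as follows: "logistic regression model with study arm as the primary predictor and enrollment site and cancer stage (AJCC stage III or IV) as the covariates". What is reported is the arm coefficient: "The exponentiated coefficient for the study arm will estimate the odds ratio of ACP". The rule at issue then follows: "Any other covariates that are differentially distributed by study arm will also be included in the model for adjustment". The section does not say which covariates are candidates, what counts as a difference, or whether a covariate must be related to ACP.

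The pool is wide. Under Data collection, "Baseline demographics, medical history, performance status, and disease characteristics will be obtained from EMR review", and Table 4 also lists a full set of baseline surveys. The Additional analyses section plans none, so no fixed-covariate result is set beside the primary one.

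On timing, the Allocation section has unblinded coordinators randomise straight after enrolment. The Participant timeline section places baseline record review and surveys after allocation, and Data collection allows a week from enrolment. The Blinding section states that participants and coordinators know the allocation.

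**The concern.** The rule selects covariates for a reason unrelated to their value in the model. In a randomised comparison, a difference in a true pre-allocation variable is chance. Adjusting for it helps only if the variable predicts ACP, and the rule does not ask that. A strongly prognostic variable that happens to balance is left out.

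Two consequences matter. First, the odds ratio is non-collapsible: the true value changes with the set of prognostic covariates conditioned on, even under perfect balance. A data-dependent set therefore means a data-dependent estimand. Second, the criterion can be read in several ordinary ways (a p-value, a standardised difference, visual judgement), and these lead to different primary results from the same data.

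There is also a narrower point. A survey labelled baseline but answered after the participant knows the allocation may already reflect it. A rule that looks for differences by arm would pick out exactly such a variable and adjust part of the effect away.

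**Working it through.** **Inputs from the Sample size and Allocation sections.** 1:1 allocation; "With an alpha of 0.05 and power of 90" per cent; control rate 30% ("conservatively assuming that 30% of patients in the enhanced standard care arm will have ACP"); a 30-point difference, so 60% under intervention; 20% attrition; 160 patients, so 80 per arm and 80 × 0.8 = 64 per arm with outcome.

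**The plan's own figure.** Two-sided, pooled variance, mean rate 0.45:
n = [1.960·√(2·0.45·0.55) + 1.282·√(0.3·0.7 + 0.6·0.4)]² / 0.3² = (1.379 + 0.860)² / 0.09 ≈ 55.7, so 56 per arm; 56/0.8 = 70. The figures reproduce. At 64 per arm the same comparison has 93.6% power.

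**How often the rule acts.** The protocol gives neither the number of candidates (k) nor a threshold; both are assumed here. For independent candidates, P(at least one enters) = 1 − (1 − a)^k.

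| Criterion | k=5 | k=10 | k=15 | k=20 |
|---|---|---|---|---|
| p<0.05 | 23% | 40% | 54% | 64% |
| p<0.10 | 41% | 65% | 79% | 88% |

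With a standardised-difference criterion at 80 per arm, the standard error is √(2/80) = 0.158. A cut-off of 0.2 is exceeded with probability 0.206 per variable, so 1 − 0.794^10 = 90% for k=10. A cut-off of 0.1 gives 1 − 0.473^10 = 99.9%.

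**How far the target can move.** The crude odds ratio is (0.6/0.4)/(0.3/0.7) = 3.5. Given two independent prognostic covariates, the same 30% versus 60% contrast is a conditional odds ratio of 4.5 (log-OR 0.7 per SD each) or 5.6 (1.0 per SD each).

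**How much the reading matters.** Four criteria (p<0.05, p<0.10, standardised difference 0.2 and 0.1) were applied to the same simulated trials: 64 per arm, 10 candidates, two of them prognostic, 3,000 replicates. The largest and smallest odds ratios from one dataset differed by a median factor of about 1.2 to 1.3, and by 1.7 to 2.2 at the 90th percentile.

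**Power and error.** Simulation at 30% versus 60%, 64 per arm, 10 candidates of which two are prognostic, 4,000 replicates (Monte Carlo error about 0.4 points, from √(0.94·0.06/4000)):

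| Model | Power, 0.7 per SD | Power, 1.0 per SD | Mean SE of log-OR |
|---|---|---|---|
| Arm, site, stage | 93.4% | 93.2% | 0.39 |
| Same plus the rule (p<0.05) | 93.6% | 94.0% | 0.40 |
| Same plus both prognostic covariates | 96.4% | 97.7% | 0.45–0.50 |

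With no true effect, the rule rejected in 4.3% to 4.9% of trials, against 5.0% to 5.8% for the fixed list. A variant with one prognostic and nine noise covariates gave about 92% without the sentence, about 93% with it, and 96–98% with the prognostic covariate fixed. Across both set-ups, fixing prognostic covariates gains about 3 to 6 points, measured against the rule or against site and stage alone.

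**The case against.** The strongest case for the plan is that little harm can be shown. Site and stage are already fixed, the test keeps its size, and the sentence leaves power where it was. At p<0.05 the rule barely moves the average estimate (median odds ratio 3.7 without it, 3.7 to 3.8 with it). A fuller covariate list may sit in a full protocol or analysis plan that is not shown, and its absence from an article is no fault. All of this stands. What remains is a positive rule, stated for the primary model, that says how further covariates are chosen.

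Several stronger readings are tempting and are not supported.

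- **A large loss of power.** With a conditional log-OR of 1.0 and one strong covariate (1.5 per SD), the rule gave 49% power and always adjusting gave 65%. But at a 30% control rate that is only about 30% versus 47%, well short of the planned contrast. In a separate check at that effect, the model without the sentence had 48.4% and the rule 47.8%. The gap comes from not naming prognostic covariates.
- **A loss of precision.** In logistic regression, adjustment for prognostic covariates raises the standard error of the log-OR. It is power that improves.
- **Selection after unblinding.** The Blinding section keeps the lead statistician blinded. Covariates could be selected under masked arm labels and without outcomes. The protocol does not say so, but neither does it say the choice follows sight of the results.
- **Baseline differences are treatment effects.** This is possible for surveys answered after allocation. It is much less plausible for demographics and history taken from the medical record.

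**Conclusion.** The point holds as one about an undefined primary estimand and avoidable discretion. It does not threaten the validity of the test or the sample size. The parts that rest on the document alone are that selection is by observed difference, that no list or threshold is given, that the effect measure is a conditional odds ratio, and that baseline surveys follow open allocation. The sizes rest on assumptions: the number and independence of candidates, the thresholds, and the strength of the prognostic covariates. The power comparison assumes p<0.05; other readings of the criterion would shift it. The change is worth making because it is cheap and settles what the primary result is.

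**What to change.** Delete the sentence from the primary model. Fix the covariates now: arm, site, stage and a short list chosen because it is expected to predict ACP and is already collected from the medical record, for example age and performance status. Include ACP status only as documented in records dated before allocation. The self-reported baseline item should not be used, since it is collected after allocation. Check prior ACP for near-separation, because an existing directive may by itself satisfy the 6-month outcome. Keep any adjustment for observed imbalance as a sensitivity analysis, labelled as such, with its criterion stated.

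The cost is a short edit before data are compared by arm, with no new data collection and no change to 56, 70 or 160. The downsides are small. The reported odds ratio is conditional on the fixed list, and its standard error is somewhat larger (0.45–0.50 against 0.39 in the simulations). The list should stay short: at 64 per arm the median estimate with two added covariates ran above the true value (5.0 against 4.5, and 6.2 against 5.6).
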